### Intervention

The intervention group will take two capsules of synbiotic per day (one capsule after lunch and one after dinner), and the control group will take two capsules of placebo (containing 500 mg lactose, magnesium stearate, and talc) per day at the same times for 12 weeks. The synbiotic and placebo capsules look and smell identical and will only be differentiated by a label “A” or “B” on the box. The boxes will be labeled by a third party who is not involved directly in this study. Each synbiotic capsule (Familact, produced by Zisttakhmir Company, Tehran, Iran) contains 500-mg levels (109 colony-forming units [CFUs]) of seven beneficial bacteria (*Lactobacillus casei* 3 × 10^8^ CFU/g, *Lactobacillus acidophilus* 2 × 10^8^ CFU/g, *Lactobacillus bulgaricus* 2 × 10^9^ CFU/g, *Lactobacillus rhamnosus* 3 × 10^8^ CFU/g, *Bifidobacterium breve* 2 × 10^8^ CFU/g, *Bifidobacterium longum* 1 × 10^9^ CFU/g, and *Streptococcus thermophilus* 3 × 10^8^ CFU/g), along with a prebiotic fructooligosaccharide (contributing to the growth and activity of probiotics) and other components (lactose, magnesium acetate, talc). Each box contains 30 capsules. Participants will be given six boxes for the entire 3-month intervention (two boxes at the beginning of each month). Moreover, patients will continue to take diabetic medication during the study. The Diabetes Clinic Center in Yazd and Shahid Sadoughi University of Medical Sciences will be responsible to follow up any reports from participants for any potential relevant issues and adverse events. Any possible adverse events will be reported to the medical ethics committee throughout the study. Participants will be informed at the beginning of the study via the consent form that they have the right to withdraw from the study at any time for any reason or even for no reason.

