### Randomization and blinding

The present study is a two-arm, double-blind parallel RCT in which participants will be randomized 1:1 using the method of stratified block randomization based on age (25–45 and 45–65 years) and sex (male and female), so that the number of samples assigned to each of the groups will be equal [47, 48]. To randomly allocate eligible individuals to the intervention and control groups, computer-generated random numbers will be used, enclosed in sealed envelopes by a third person who will not be involved in the study. Capsules containing the synbiotic and placebo are similar in shape and appearance and will be packed in the same boxes (in terms of color and shape). The capsule boxes will be labeled with codes “A” and “B” by a third party who has no direct involvement in the study. Both participants and investigators will be blinded to the content of the boxes, allocation, and study treatment until data analysis.

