### Adherence

Adherence to the intervention will be monitored every day through phone interviews. Written and verbal instructions on how to take the capsules will be provided at the first visit and at each following visit. Individuals will be asked to take one capsule after lunch and one after dinner, which also will improve their adherence to the intervention. Moreover, participants will be asked to record their daily consumption of supplements or placebos in the study diary. All participants will be asked to return any remaining capsules in the boxes to the next visit. At the end of the 12-week intervention, if the number of remaining capsules for each participant is more than 10% of the total administered capsules (*n* = 18), that participant will be classified as non-adherent. All participants, both adherent and non-adherent, will follow the same schedule.

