### Outcomes

The primary outcomes consist of expression of miR-126 and miR-146a, the gut microbiome status, and serum level of TNF-α. Secondary outcomes will be serum levels of lipid profiles (TG, total cholesterol, HDL-C, and LDL-C), anthropometric data, fasting plasma glucose level, HbA1c, fasting plasma insulin level, insulin sensitivity (quantitative insulin sensitivity check index [QUICKI]), homeostasis model assessment of insulin resistance (HOMA-IR), and homeostasis model assessment of beta cell function (HOMA-B). All these factors will be measured at onset and end of the study.

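### The only adverse-event route described is follow-up of participants' reports, and the daily calls are described for adherence alone, so mild events are likely to be under-recorded

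*Protocol article*

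**What the plan says.** Adverse events appear in two sentences of the protocol article's Intervention section. The first says the Diabetes Clinic Center and the university "will be responsible to follow up any reports from participants for any potential relevant issues and adverse events". The second sends them onward: "Any possible adverse events will be reported to the medical ethics committee throughout the study".

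The Adherence section describes frequent contact with participants, each time for capsule-taking:

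- Phone: "Adherence to the intervention will be monitored every day through phone interviews".
- Visits: "Written and verbal instructions on how to take the capsules will be provided at the first visit and at each following visit". Leftover capsules are also returned at visits.
- Diary: "participants will be asked to record their daily consumption of supplements or placebos in the study diary".

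The Outcomes section begins "The primary outcomes consist of expression of miR-126 and miR-146a, the gut microbiome status, and serum level of TNF-α" and continues with lipid, anthropometric and glycaemic measures. No safety or tolerability outcome is listed. The Statistical analysis section mentions no summary or comparison of adverse events. On blinding, the article states: "Both participants and investigators will be blinded to the content of the boxes, allocation, and study treatment until data analysis".

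**The concern.** The harms sentence starts from the participant: a report comes in and the site follows it up. A team working from this text alone would run a participant-initiated system while speaking to every participant each day about something else.

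This matters for these capsules. Both contain lactose, and the active one adds seven live bacterial strains and fructooligosaccharide. The Background describes prebiotics as fermentable fibres. Mild gut symptoms are therefore plausible, and people often do not volunteer such symptoms unless asked.

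Three things are at stake:

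- A short or empty list of complaints could be read as good tolerability when it reflects the way events were gathered.
- The leftover-capsule count that defines non-adherence cannot by itself separate intolerance from forgetting. That weakens the planned comparison of intention-to-treat and per-protocol results.
- The Discussion hopes that valid results will contribute to better treatment of diabetes. A reader would want tolerability data alongside the benefit.

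**Working it through.** **No figure to reproduce.** The article gives no adverse-event rate, capture rate or safety power. The check sets the text side by side and then illustrates the size with assumed rates.

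**Step 1. What each contact is for, as described**

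| Contact | Section | Stated purpose | Adverse events mentioned? |
|---|---|---|---|
| Participant report | Intervention | Follow-up, then ethics committee | Yes |
| Daily phone interview | Adherence | Adherence | No |
| Visits | Setting, Adherence | Instructions, capsule return | No |
| Diary | Adherence | Capsule intake | No |

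Participant report is the only route described. Nothing says it is the only route used.

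**Step 2. Inputs.** From the article: 36 enrolled per arm, 72 in total, 12 weeks = 84 days, daily calls. That makes 72 × 84 = 6,048 planned participant-contacts on which a question could be carried. Assumed, because the article gives nothing: true incidence *p* and the fraction of events recorded *s*.

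**Step 3. Recorded events in one arm.** Participants with a recorded event = 36 × *p* × *s*. The chance of recording none = (1 − *p* × *s*)^36.

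| *p* | *s* | Expected recorded | Chance of none |
|---|---|---|---|
| 20% | 20% | 36 × 0.04 = 1.44 | 0.96^36 = 23% |
| 20% | 60% | 36 × 0.12 = 4.32 | 0.88^36 = 1.0% |
| 20% | 100% | 7.2 | 0.80^36 = 0.03% |
| 10% | 20% | 36 × 0.02 = 0.72 | 0.98^36 = 48% |
| 10% | 60% | 36 × 0.06 = 2.16 | 0.94^36 = 11% |
| 10% | 100% | 3.6 | 0.90^36 = 2.3% |

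The result depends strongly on *s*. An empty list despite real events is quite possible at 20% capture. At 60% capture it is unlikely if incidence is 20%.

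**Step 4. Comparison of arms when capture is equal.** The recorded rates are *s* × *p*1 and *s* × *p*0. The risk ratio is (*s* × *p*1)/(*s* × *p*0) = *p*1/*p*0, which does not depend on *s*. The risk difference is *s* × (*p*1 − *p*0), which shrinks with *s*. Power (two-sided 5%, normal approximation, *n* = 36 per arm) is Φ[(Δ − 1.96 × √(2m(1 − m)/n)) / √((a(1 − a) + b(1 − b))/n)], where a and b are the recorded rates, m their mean and Δ = a − b.

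Worked case, true rates 30% and 10%:

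- *s* = 1: Δ = 0.20; (0.20 − 1.96 × 0.0943)/0.0913 = 0.17; power 57%.
- *s* = 0.5: Δ = 0.10; (0.10 − 1.96 × 0.0707)/0.0697 = −0.55; power 29%.

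| True rates | *s* | Risk ratio | Risk difference | Power |
|---|---|---|---|---|
| 30% v 10% | 100% | 3.0 | 20 points | 57% |
| 30% v 10% | 75% | 3.0 | 15 points | 43% |
| 30% v 10% | 50% | 3.0 | 10 points | 29% |
| 30% v 10% | 25% | 3.0 | 5 points | 16% |
| 40% v 10% | 100% | 4.0 | 30 points | 85% |
| 40% v 10% | 50% | 4.0 | 15 points | 49% |

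Equal under-capture costs absolute rates and power. It does not bias the risk ratio.

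**The case against.** The strongest objection is that this is inferred from silence. The Intervention sentence assigns responsibility for follow-up. It does not say only, and a participant's report may be an answer to a question. The sentence on the ethics committee is not limited to volunteered events. The calls sit under a heading about adherence, so describing them for that purpose is natural. The article condenses a fuller protocol, and its SPIRIT schedule figure and additional file are not shown. Questioning scripts, log forms and safety tables are often left to such documents.

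Much of this stands. A reader might infer that events will be collected only when volunteered, or that none of the calls will include a question about them. The article supports neither. Nor does it show that a summary by arm is ruled out. What survives is that the article does not leave harms wholly unmentioned: it names a route, and that route begins with the participant. It also gives a specific purpose to every other contact, and none concerns harms.

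A second objection is that blinding, look-alike capsules and one procedure for both arms make differential reporting unlikely. This also stands. A reader might conclude that the arms cannot be compared on tolerability, but step 4 shows that the ratio is preserved under equal capture. Everyone in an arm shares one visible box code, so an impression of one letter could form. That is a risk, not a demonstrated bias.

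Third, the illustrative rates are assumptions, and the 23% and 48% figures use the lowest capture value. That is correct, so the range is shown. The 100% rows are a ceiling that one added question would not fully reach.

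**Conclusion.** The point holds in a limited form. The only adverse-event route the article describes is follow-up of participants' reports. The calls, diary and visits are described for capsule-taking alone, and no adverse-event outcome or comparison by arm is named. Followed as written, mild events are likely to be under-recorded.

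The consequence is loss of absolute rates and power, not loss of the comparison. Capturing half the events halves the risk difference and, at assumed rates of 30% and 10%, takes power from 57% to 29%. The chance of an empty list in an arm runs from about 1% to 48% over assumed incidences of 10% to 20% and capture of 20% to 60%. No capture rate can be taken from the article.

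A reader might also infer that serious events would be recognised late. The article does not show this, since daily contact gives each participant a daily chance to speak up.

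The change is worth making because it is cheap and harms data not collected at the time are hard to recover. It does not affect the validity of the primary outcomes.

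**What to change.** Add one fixed, non-leading question to the existing phone calls and to each visit after baseline, such as whether there has been any new symptom or illness since the last contact. Use the same wording in both arms. Log onset, duration, severity and seriousness while blind to allocation. Add adverse events to the Outcomes section and tabulate them by arm for all randomised participants.

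If the full protocol already solicits events, say so in the Intervention section and state when and how.

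The cost is one question in contacts already planned, one log form and one table. The small downside is that more minor events will have to be logged and reported to the ethics committee. Recruitment was still under way at publication. If the question starts part-way through, record the start date so that events found before and after it can be shown separately.

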### Adherence

Adherence to the intervention will be monitored every day through phone interviews. Written and verbal instructions on how to take the capsules will be provided at the first visit and at each following visit. Individuals will be asked to take one capsule after lunch and one after dinner, which also will improve their adherence to the intervention. Moreover, participants will be asked to record their daily consumption of supplements or placebos in the study diary. All participants will be asked to return any remaining capsules in the boxes to the next visit. At the end of the 12-week intervention, if the number of remaining capsules for each participant is more than 10% of the total administered capsules (*n* = 18), that participant will be classified as non-adherent. All participants, both adherent and non-adherent, will follow the same schedule.

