## Materials and methods

### Study design

This study is a randomized, double-blind, placebo-controlled, parallel clinical trial conducted at the Diabetes Clinic Center in Yazd, Iran. Patients with T2DM will be randomly assigned to a treatment or control group (*n* = 36/group) and will receive either a daily synbiotic (1000 mg) or placebo, respectively, for 12 weeks. An overview of the study is presented in Fig. 1. The Standard Protocol Items: Recommendations for Interventional Trials (SPIRIT) checklist was used to detail the study protocol [46] (see Additional file 1). A SPIRIT diagram including the timepoints of the study is shown in Fig. 2. Any methodological changes in the study design which could affect study procedures or participants’ safety will be discussed by the ethics committee before the study is conducted.

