### Statistical analysis

Statistical analyses will be performed with SPSS software V.23.0 (SPSS Inc., Chicago, IL, USA). Normality of distribution of data will be assessed by the one-sample Kolmogorov-Smirnov test. At first, the primary information of the intervention and control groups will be compared. Continuous data will be presented as means ± standard deviation (SD), and categorical data will be expressed as numbers and percentages. The independent samples *t* test and the Mann-Whitney *U* test will be used for analyzing the differences in parametric continuous and asymmetric variables between the two groups, respectively. The paired *t* test will be used to identify the effect of the intervention in each group. General linear models will be applied to analyze the effects of the synbiotic relative to placebo after adjusting the baseline factors and individuals’ characteristics. The intention-to-treat (ITT) method and the per protocol analysis will be applied for data analysis. The former considers all participants in the trial and ignores anything that happens after randomization such as misallocation and non-compliance. The latter is adjusted for actual treatment. The results of the aforementioned analyses will be compared with each other.

*P* values < 0.05 will be considered as statistically significant.

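### The non-adherence cut-off of 18 leftover capsules is 10% of the 180 dispensed, but only 168 fall due in 12 weeks, so the working tolerance is 3.6% of doses, not 10%

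*Protocol article*

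**What the plan says.** All statements are in the protocol article.

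- **Daily intake** (Intervention): "The intervention group will take two capsules of synbiotic per day (one capsule after lunch and one after dinner"; the control group takes two placebo capsules "per day at the same times for 12 weeks".
- **Duration** (Study design): participants "will receive either a daily synbiotic (1000 mg) or placebo, respectively, for 12 weeks".
- **Supply** (Intervention): "Each box contains 30 capsules", and "Participants will be given six boxes for the entire 3-month intervention (two boxes at the beginning of each month".
- **Adherence rule** (Adherence): leftovers are judged at the close of the 12 weeks. A participant is non-adherent if the number of "remaining capsules for each participant is more than 10% of the total administered capsules", which the section gives as 18. Adherent and non-adherent participants follow the same schedule.
- **Analysis** (Statistical analysis): both an intention-to-treat and a per-protocol analysis are planned and will be compared. Of the per-protocol analysis the article says only: "The latter is adjusted for actual treatment".

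**The concern.** The rule takes its denominator from a supply that lasts 90 days but makes its count at 84 days. Leftover capsules measure missed doses only if every dispensed capsule was due. Here 12 were never due, yet the rule counts them as if they had been missed, and they use up two-thirds of the allowance of 18 before a single dose is missed.

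The article contains no other adherence classification. Followed as written, it would make the trial report poorer adherence than occurred. It would also affect the per-protocol analysis if that analysis selects participants by this class.

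**Working it through.** **Inputs from the article**
- Boxes dispensed: 6; capsules per box: 30 (Intervention).
- Capsules per day: 2 (Intervention).
- Duration: 12 weeks = 84 days (Study design, Intervention, Adherence).
- Cut-off: more than 18 left (Adherence).

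**Reproducing the plan's figure**
- Dispensed = 6 × 30 = 180, and 10% × 180 = 18. This matches the stated 18.
- The other possible base does not: 10% × 168 = 16.8.

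**Capsules due and surplus**
- Due = 2 × 7 × 12 = 168.
- Left after perfect intake = 180 − 168 = 12.
- Missed doses allowed before the label applies = 18 − 12 = 6, and 6/168 = 3.6%.

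**What the rule does**, with taken = 180 − left and the percentage = taken/168:

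| Left | Taken | Missed | % of due taken | Class as written | Class if the limit is 10% of due |
|---|---|---|---|---|---|
| 12 | 168 | 0 | 100.0 | adherent | adherent |
| 18 | 162 | 6 | 96.4 | adherent | adherent |
| 19 | 161 | 7 | 95.8 | non-adherent | adherent |
| 28 | 152 | 16 | 90.5 | non-adherent | adherent |
| 29 | 151 | 17 | 89.9 | non-adherent | non-adherent |

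The two rules disagree for 19 to 28 capsules left, which is 7 to 16 missed doses (7/168 = 4.2% to 16/168 = 9.5%).

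**When the cut-off would be right.** Over 90 days, 2 × 90 = 180 capsules are due and none are surplus. Then 18 left is 18/180 = 10.0% missed, and 19 left is 161/180 = 89.4% taken.

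**How many participants this could affect.** The article gives no expected missed-dose rate, so this step rests on assumption. Missed doses are taken as beta-binomial with n = 168, a mean missed rate from 1% to 8%, and concentration 20 or 50 for the spread between patients. The share labelled non-adherent is P(missed > 6) as written and P(missed > 16) under 10% of due.

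| Assumed mean missed | As written | 10% of due |
|---|---|---|
| 1% | 6–8% | 0.3–1.5% |
| 2% | 16–17% | 1–4% |
| 3% | 27–29% | 3–7% |
| 5% | 47–56% | 10–15% |
| 8% | 70–83% | 30–31% |

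With 36 per arm, the 5% row is about 17 to 20 participants per arm against about 3 to 5. The 1% row is about 2 to 3 against fewer than 1.

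**The case against.** **The rule agrees with itself.** It names the capsules given out as its base, and 18 is exactly 10% of 180. Nowhere does the article say that 10% of due doses is the intended tolerance. This is fair as a reading of the words, and the intent is an inference. But a count of untaken capsules serves as a measure of adherence only against what should have been taken, and nothing in the article allows for the 12 surplus capsules.

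**Twelve weeks may be a loose label for three monthly cycles.** Two boxes a month at two capsules a day is exactly 30 days' supply, and six boxes is 90 days. On that reading the cut-off works. Against it, the Study design, Intervention and Adherence sections all say 12 weeks, and the Adherence section times the count at the end of those 12 weeks. Reading a month as four weeks does not help: each cycle dispenses 60 and uses 56, so 12 are still left after three cycles.

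**The effect on the per-protocol analysis is not established.** This stands. A reader might infer that the per-protocol set will shrink sharply and that its comparison with intention to treat will be distorted. The article never says that the set is defined by this capsule count. Its one sentence on the subject refers to actual treatment, and how the adherence class enters, if it does, is not stated. Whether that sentence describes a per-protocol or an as-treated analysis is a separate question that adds nothing to the capsule arithmetic.

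**The large percentages depend on assumed missed-dose rates.** This also stands. The plan includes daily telephone contact and a diary, so low rates are plausible, and at a 1% mean the gap is a few percentage points.

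**Conclusion.** The cut-off is wrong as written for a 12-week intervention with six boxes dispensed. It labels participants non-adherent from the seventh missed dose (95.8% of due doses taken), so the tolerance is 3.6% rather than 10%. That result needs no assumption beyond the article's own figures, a count made at day 84, and capsules not returned being counted as taken.

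The certain consequence is that reported adherence is understated. Wrongful exclusion from the per-protocol analysis follows only if that set uses this class. The number of participants affected is illustrative and ranges widely with the assumed missed-dose rate.

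Severity is minor to moderate. A reader might take this as a threat to the trial's main result, but the documents do not support that: intention to treat keeps all participants and disregards non-compliance, and neither the primary outcomes nor the sample size uses the cut-off. The raw counts are collected, so adherence can be re-expressed against doses due without loss of data.

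**What to change.** 1. Reconcile the 12-week duration with the 3-month description and the six-box supply, so that the number of capsules due is unambiguous.
2. Define non-adherence against capsules due: more than 10% of the capsules due between first dose and final visit not taken. If 84 days and 180 dispensed both stand, 180 − 0.9 × 168 = 28.8, so 29 or more returned is non-adherent. Tying the rule to each participant's own dates also covers final visits that are early or late.
3. State whether the per-protocol set uses this classification.

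The cost is a sentence or two in the protocol or analysis plan. Returned capsules are already counted, so no new data are needed, and the change is best made before unblinding.
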